#### Interim analyses {21b}

A single primary analysis will be performed. No interim analysis is planned in the current study.

#### Methods for additional analyses (e.g., subgroup analyses) {20b}

Subgroup analyses will be performed within the following groups: age (< 35/≥35 years) and additional moderate-intensity exercise (Y/N). The statistical significance level will be set at 5%. Heterogeneity of treatment effects among subgroups will be tested by interactive subgroup analysis.

### Oversight and monitoring

#### Composition of the coordinating center {5d}

The principal investigator leading all coordinating centers designed this trial. For each center, a principal investigator is delegated respectively. They are responsible for the refinement of the protocol, the CRF, and other materials. Personnel-wise, they construct a steering team (see the section below) and recruit staff to run the trial. They organize weekly and monthly meetings for quality control. All staff convened to the study, including PI themselves and other healthcare providers, research coordinators, and data analysts, will contribute to the smooth operation of the whole process.

#### Composition of the trial steering committee and data monitoring committee {5d, 21a, 23} and frequency and plans for auditing trial conduct {23}

Oversight on safety, data quality, and financial management will be provided by the Ethics Committee and the Clinical Trial Research Center in the academic hospitals, as well as the staff in the PROSPECT study. The study protocol undergoes reviews and approval by the hospital Ethics Committee prior to its launch. Any modification to the protocol should be submitted and approved before continuation of the study. The Ethics Committee also demands principal investigators to hand in research progress reports. Audits to monitor data management are carried out by the quality assurance (QA) department of Clinical Trial Research Center once a year, where investigators of the study are masked. Advice is returned to PIs and their revision will be followed in later meets. These committees are mainly based on hospitals. Funders are not implicated in the trial design and conduct, nor are they involved in the supervision. No competing interests are present concerning this study.

#### Adverse event reporting and harms {22}

Adverse events are defined as worsening of existing POP or newly developed symptoms related to PFDs while serious adverse events are defined as affecting normal daily life. As extensively used treatments in clinical practice, side effects and adverse events of PFMT and NMES are scarcely observed. However, some patients do feel pain or discomfort with NMES. Adverse events of vaginal symptoms, back and abdominal pain, short of breath, and chest pain have been reported in POP patients treated with PFMT although considered irrelevant to the intervention. For safety concerns, participants assigned PFMT with NMES and EMG biofeedback device are all called to the hospital settings for its use, allowing us to closely monitor complications. Whatever unexpected is experienced by the participants, we will assess (1) whether it has been already identified, (2) whether it is related to the intervention procedure, and (3) whether it subsides after the cessation of the intervention. Regardless of the severity, such events are recorded on the Adverse Events Report Form with the time of onset, seriousness, duration, measures undertaken, and results. The forms will soon be transferred to the principal investigator and the Ethics Committee.

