### Strategies to improve adherence to interventions {11c}

Education on the roles pelvic support plays in POP as well as the impact of its progression on individual lives will be incorporated into the postpartum clinic and research appointments. With controlled training by NMES in the hospital scene and visualization of performance through EMG biofeedback, instrumented PFMT is theoretically motivative in nature. Encouragement from professionals can also raise participants’ self-efficacy. Thus, adherence to conventional PFMT could be enhanced by the timely response to their training records. Monthly calls will enable researchers to monitor their obedience and meanwhile collect encountered obstacles to hopefully overcome by optimizing study design.

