### Statistical methods

#### Statistical methods for primary and secondary outcomes {20a}

All statistical analyses will be carried out according to the Statistical Analysis Plan and Health Economic Analysis Plan. The primary analysis will be performed at the time right after intervention and at the end of the trial when a 36-month follow-up has been completed. The independent data monitoring and ethics committee (DMEC) will review confidential interim analyses of accumulating data at its discretion, at least annually. The primary effectiveness analysis will be based on the intention-to-treat (ITT) principle.

In the analysis of the primary outcome, we will use the chi-square test to compare the proportion of participants showing improvement of at least 1 level of POP-Q staging among experimental and control groups right after intervention. Furthermore, a binary logistic regression model will be adopted to adjust potential covariate variables like the newborn weight, the length of first/second stage, infant head circumference and the maternal body mass index, etc. For analysis of secondary outcomes, we used appropriate models: the multilevel mixed models for continuous outcomes (PFDI-20, PFIQ-7, PISQ-12, and ICIQ SF-7 scale scores, pelvic floor muscle electromyography values, VAS and QALY of each incremental cost) for the repeated measurements at 6, 12, 24, and 36 months, chi-square test and logistic regression for categorical outcomes (POP-Q staging, pelvic floor muscle strength). The safety index (AE incidence) was analyzed with the chi-square test.

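### The adverse event definition does not cover the stimulation pain the protocol itself expects, and the event set behind the AE incidence test is not fixed

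*Protocol article*

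**What the plan says.** All of the following come from the protocol article.

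- **Definition** (Adverse event reporting and harms {22}): "Adverse events are defined as worsening of existing POP or newly developed symptoms related to PFDs".
- **Seriousness.** For the graver category, the same section gives one criterion only: "serious adverse events are defined as affecting normal daily life".
- **Expected device harm** (same section): "some patients do feel pain or discomfort with NMES". No rate is given.
- **Wider use of the term** (same section): "Adverse events of vaginal symptoms, back and abdominal pain, short of breath, and chest pain have been reported in POP patients treated with PFMT".
- **Recording rule** (same section): "Whatever unexpected is experienced by the participants, we will assess (1) whether it has been already identified", followed by relatedness and whether the event resolves on stopping. Such events go on the adverse event form whatever their severity.
- **Surveillance** (same section): women given the device attend hospital for its use, "allowing us to closely monitor complications". The Experimental group section sets 24 sessions, two a week.
- **Analysis** (Statistical methods for primary and secondary outcomes {20a}): "The safety index (AE incidence) was analyzed with the chi-square test". No event set is attached to the term.
- **Shared contacts:** both arms have five appointments over the 12 weeks (Intervention description {11a}). The adherence section {11c} adds, without limiting it to one arm: "Monthly calls will enable researchers to monitor their obedience".

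**The concern.** A definition of adverse event decides what a safety comparison counts. This one is built from the condition under treatment, and the one harm the authors attribute to the experimental device is not in it. If the test follows the definition, a woman with stimulation pain and no pelvic floor symptom does not count as having had an adverse event. A woman whose prolapse progresses does count. An effective device could then look safer because it works, with its own harms left outside the comparison.

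The serious-event definition adds to this. Interference with daily life can admit a minor complaint. A medically serious event unrelated to the pelvic floor would first fail the adverse event definition.

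For any event that is counted, closer observation of one arm could raise that arm's recorded incidence without a true difference. This trial is meant to inform wider use of the device, so its safety table needs a fixed meaning.

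**Working it through.** **1. Which events are tested?** Section {22} offers three scopes:

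- The formal definition covers prolapse worsening and new pelvic floor symptoms. NMES pain is not named.
- The wider usage takes in back, abdominal and chest pain and shortness of breath, most of which fall outside the formal definition.
- The recording rule covers anything unexpected. NMES pain is expected, so its inclusion is not assured.

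Section {20a} does not choose between them. The discontinuation criteria {11b} list adverse events separately from other unintended responses, which fits the narrow scope. The natural reading is therefore that the test uses the formal definition, but the text does not settle it.

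**2. Overlap with efficacy.** The primary outcome {12} is improvement of at least one POP-Q stage, and the symptom proportions are secondary outcomes. A woman's stage can improve, stay the same or worsen. Worsening uses the same staging but is not the complement of improvement, so the overlap is partial.

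**3. Number of women outside the count (illustration).** The plan gives no AE figure to reproduce. The arm size used here is 142, from Sample size {14}, and it does reproduce: [0.5×0.5 + 0.2×0.8] × (1.645 + 0.842)² / (0.30 − 0.15)² = 113 per arm, and 113 / 0.8 = 142 after attrition. The pain rate is assumed to be 5–20% of women without another counted event:

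- 142 × 0.05 = 7 women
- 142 × 0.20 = 28 women

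The choice of event set could also change the direction of the result. Assume pelvic floor events in 10% of the NMES arm and 20% of controls, with independent stimulation pain in the NMES arm only. The wide NMES rate is 1 − 0.90 × (1 − pain):

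- 5% pain: 14.5%
- 10% pain: 19%
- 20% pain: 28%

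The comparison with 20% reverses at a pain rate of 1 − 0.80/0.90 = 11%.

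**4. Would a counted difference be visible?** Take rates a and b with mean p and n = 142 per arm, SE0 = √(2p(1−p)/n) and SE1 = √((a(1−a)+b(1−b))/n). The rejection probability at two-sided 5% is Φ((d − 1.96·SE0)/SE1) + Φ((−d − 1.96·SE0)/SE1), where d = |a − b|. For an assumed 10% v 1%, SE0 = 0.0271 and SE1 = 0.0265, so (0.09 − 0.053)/0.0265 = 1.39 and power is 0.92. Exact summation over the two binomials gives 0.96 without continuity correction and 0.92 with it.

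**5. Unequal detection (illustration).** The same formula with equal true risk in both arms gives these chances of a spurious difference:

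| True risk | Detection 90% v 90% | 95% NMES v 80% control | 90% NMES v 60% control |
|---|---|---|---|
| 10% | 0.05 | 0.07 | 0.16 |
| 20% | 0.05 | 0.10 | 0.29 |
| 30% | 0.05 | 0.14 | 0.44 |

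Every true risk and detection rate here is assumed.

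**The case against.** **Exclusion of NMES pain is not certain.** A reader might infer that the known harm will go uncounted. Section {22} does not support that as fact. It records events whatever their severity, it asks whether a reaction is already identified (which makes sense only if known reactions can be assessed), and some pelvic pain could pass as a pelvic floor symptom. The data collection forms are said to be attached to the protocol and are not shown, and neither is the analysis plan. What remains is a conflict between definition and recording rule, and a tested event set that this document leaves open.

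**Worsening is not the primary outcome in reverse.** That reading is tempting, but an unchanged stage is neither improvement nor worsening. Only a partial overlap stands.

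**Unequal detection is not established.** The Control group section says physiotherapists check uploaded training records daily and claims the same contact and supervision as in the experimental arm. POP-Q staging, symptom enquiry and questionnaires are scheduled identically at follow-up in both arms {18a}, and pelvic floor assessors are blinded {17a}. For narrowly defined events this limits the bias. Surveillance matters more under the wide event set, but under that set NMES pain would also be counted. The two problems therefore do not both apply at full strength. Still, the control training record lists only contraction and relaxation times, repetitions and sets, and names no symptom item. Equal contact does not show equal enquiry about harms.

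**The serious-event definition is secondary.** No test of serious events is described, so this affects reporting rather than the chi-square comparison.

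**Conclusion.** The concern holds in limited form. Section {22} fixes an adverse event definition that omits the device harm it goes on to name, and that conflicts with its own usage and recording rule. Section {20a} then tests AE incidence without saying which set applies. On the natural reading, the only safety test stated in the article can miss stimulation pain and partly repeats the POP-Q and symptom outcomes. The serious-event definition is not tied to medical seriousness.

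Ascertainment may differ between arms, but the direction and size of any net bias are unknown. The 7–28 women and the 7–44% spurious rejection rates rest wholly on assumed pain, risk and detection rates. They show how the fault could act in a trial of this size. They do not show that the AE comparison is uninterpretable, which a reader might otherwise conclude. The efficacy analysis is unaffected. The change should be made because it is cheap and the safety result depends on it.

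**What to change.** - Define an adverse event as any untoward medical occurrence after randomisation, whether or not related to treatment, with a prespecified category for stimulation-related pain and discomfort.
- Define serious adverse events by standard medical seriousness criteria.
- Make the recording rule in {22} and the event set tested in {20a} match that definition, so that expected reactions are recorded as well as unexpected ones.
- Report worsening of prolapse or pelvic floor symptoms separately from other adverse events.
- Base the between-arm test on the same adverse event questions asked at contacts common to both arms: the five appointments, the monthly calls and the follow-up visits. List events noted only at NMES sessions separately.

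The cost is revised wording in the protocol and analysis plan and a small change to the adverse event form, with no new visits. The downside is that the experimental arm's adverse event count may look higher.

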## Background and rationale {6a}

Pelvic organ prolapse (POP), encompassed in the spectrum of pelvic floor dysfunction (PFD), is a common condition characterized by a descent of the female pelvic organs (bladder, uterus, and rectum) from the normal anatomic position into or through the vagina [1]. Half parous women have varying degrees of POP, and one in 12 women suffered from bothersome POP symptoms [2] which negatively influence women’s social, physical, and psychological well-being [3]. Direct medical cost for PFDs is estimated to total $412 million for ambulatory care and $1012 million for POP surgery annually in the USA [4]. The number of patients in need of POP treatment is on a rapid rise due to an aging population and an improving awareness [5]. Treatment for POP includes conservative options (like pelvic floor muscle training, PFMT) and surgery. The former is recommended for all POP patients and particularly helpful for those with a mild to moderate degree of prolapse [6–8], while the latter is reserved for those having severe symptomatic prolapse with the goal of anatomical restoration and symptom relief [1]. Given the substantial societal and economic burden, there is a growing demand to identify and validate more tailored and effective treatment strategies addressing the pathogenesis of POP.

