Past medical history. We collect the gestation and delivery information for a baseline from the hospital’s Electronic Medical Record System. The important prognostic covariates for the clinical effectiveness, including newborn weight, the length of first/second stage, infant head circumference, and maternal body mass index, will be recorded.Lifestyle information: the habits of smoking or drinking, and the frequency of moderate-intensity exercise, which is important covariates for the long-term effectiveness. POP-Q stage. Anatomical severity of pelvic organ descent is measured and staged in a POP-Q examination during each follow-up appointment.Prolapse symptoms. We document the presence of POP-related symptoms among participants in each follow-up appointment. Symptoms selected for inquiry are those frequently included in the validated questionnaires and reported by POP patients.Questionnaires. POP-related urinary, colorectal-anal, and pelvic symptoms are evaluated with Pelvic Floor Distress Inventory-Short Form 20 (PFDI-20) and sexual symptoms using Pelvic Organ Prolapse/Urinary Incontinence Sexual Questionnaire (PISQ-12). The impact of such symptoms on quality of life is assessed by the Pelvic floor Impact Questionnaire-Short Form 7 (PFIQ-7), Incontinence Impact Questionnaire-Short Form 7 (IIQ-7), and EuroQol Five Dimensions Questionnaire (EQ-5D). These questionnaires are instruments with evidence of validity, reliability, and responsiveness and have been translated into Chinese. Participants are referred to complete these questionnaires at the end of each follow-up appointment.PFM strength grade. PFM strength that reflects the muscle function is graded using the Modified Oxford Scale (MOS) in digital palpation during each follow-up appointment.PFM electromyography. Glazer Protocol consists of PFM EMG values in the pre-baseline, flick contraction, tonic contraction, endurance contraction, and post-baseline phases. Obtained in each follow-up, these EMG values indicate muscle activity from an electro-physiological perspective objectively.Pelvic ultrasonography. Three-dimensional ultrasonography is widely used to assess the morphology of the pelvic floor muscles and pelvic organs, including the diameter of levator hiatus and position of the bladder and rectum at rest and during maximum Valsalva.

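### Seriousness of an adverse event is defined by effect on daily life and names no medical outcome, so a bothersome symptom of the treated condition is labelled serious

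*Protocol article*

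**What the plan says.** All the safety definitions stand in the section Adverse event reporting and harms {22} of the protocol article.

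- Adverse event: "Adverse events are defined as worsening of existing POP or newly developed symptoms related to PFDs".
- Serious adverse event: "serious adverse events are defined as affecting normal daily life". No other criterion of seriousness appears in that section or elsewhere in the article.
- Recording: anything unexpected is assessed for whether it is already known, whether it is related to the intervention, and whether it subsides when the intervention stops. "Regardless of the severity, such events are recorded on the Adverse Events Report Form with the time of onset, seriousness", followed by duration, the measures taken and the outcome. The forms go to the principal investigator and the Ethics Committee.
- Events reported elsewhere: "Adverse events of vaginal symptoms, back and abdominal pain, short of breath, and chest pain have been reported in POP patients treated with PFMT", although the article regards these as unrelated to the training.

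Two other sections bear on the point. Plans for assessment and collection of outcomes {18a} treats the effect of pelvic floor symptoms on a woman's life as an outcome: "The impact of such symptoms on quality of life is assessed by the Pelvic floor Impact Questionnaire-Short Form 7", together with IIQ-7 and EQ-5D. Statistical methods for primary and secondary outcomes {20a} plans one safety analysis, a chi-square test on adverse event incidence.

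**The concern.** Seriousness and severity answer different questions. Seriousness asks what the event led to medically; severity asks how strongly it was felt or how far it interfered with ordinary life. The article's definition uses the second question to fill the field meant for the first. The recording rule in the same section already treats them as two things, since it asks for a seriousness entry whatever the severity. Yet the only instruction for that entry is an impact threshold.

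In this trial the confusion matters more than it would elsewhere, because the adverse event definition consists of symptoms of the condition being treated. Adding an impact threshold to those symptoms makes a serious event out of ordinary disease burden. What is at stake is the usefulness of the serious label to those who receive the forms. An Ethics Committee reading it cannot tell from the label alone whether a woman was medically endangered or had a troublesome return of symptoms.

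**Working it through.** No figure in the article depends on this definition, so there is nothing to recompute. The check applies the printed definitions to typical events and compares the label with the one an outcome-based definition would give.

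| Event | Adverse event as defined? | Serious as defined? | Serious by medical outcome? |
|---|---|---|---|
| A. New or worse prolapse symptom, daily life not disturbed, no medical consequence | Yes | No | No |
| B. New or worse prolapse symptom, daily life disturbed, no medical consequence | Yes | Yes | No |
| C. Pelvic floor event leading to hospital admission | Yes | Ordinarily yes, because an admission interrupts daily life | Yes |
| D. Chest pain leading to hospital admission | No: neither prolapse nor a pelvic floor symptom | Not required, because it is not an adverse event as defined | Yes |

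**Step 1, over-labelling (B).** B is serious under the printed rule and not under an outcome-based one. It follows directly from joining the two definitions. The Background section shows that such symptoms can carry this burden: "one in 12 women suffered from bothersome POP symptoms", which it says harm well-being.

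**Step 2, loss of discrimination (B against C).** B and C receive the same label. The field does not separate a symptom flare from an event with a medical consequence.

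**Step 3, overlap with outcomes.** What makes B serious is the effect of a pelvic floor symptom on a woman's life. PFIQ-7, IIQ-7 and EQ-5D are collected at each follow-up to measure that effect and are analysed as secondary outcomes. The overlap is in content. It is not complete, because the questionnaires are summarised as average score changes whereas an adverse event needs a worsening or a new symptom.

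**Step 4, under-labelling (C and D).** C is caught in practice by the daily-life wording, though not by rule. D can escape the serious label, and the main reason is that the adverse event definition stops at pelvic floor symptoms. The section itself notes that chest pain and shortness of breath have been reported in women receiving this training, so D is not a remote example.

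**Step 5, effect on the planned analysis.** The chi-square test counts adverse events. Moving an event between serious and non-serious leaves that count unchanged.

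**The case against.** The strongest reply is that the wording is loose but does little damage. Several parts of it stand.

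- *The daily-life test is broad and misses little.* This stands largely. Death, threat to life, admission and lasting disability would ordinarily affect daily life. A reader might infer that the definition lets medically serious events go unlabelled. The daily-life wording alone does not support that; the gap comes mainly from the narrow adverse event definition.
- *Nothing is lost.* This stands. Any unexpected event is recorded and forwarded, and an admission could appear under the measures taken or the outcome. To say that a safety signal would be hidden goes beyond the text.
- *No planned comparison uses seriousness.* This stands. Only adverse event incidence is tested, and the criteria for suspending an intervention {11b} refer to adverse events or unintended responses without regard to seriousness. A reader might expect a spurious between-arm difference in serious events, but the article plans no such comparison.
- *Unblinded rating would bias the label.* Participants and treating physiotherapists know the allocation, but the article does not say who rates seriousness, so this remains conjecture.
- *The full protocol may be better.* The article refers to data collection forms and an operating manual that are not shown, and the form may carry its own criteria. That limits what can be said about classification in practice. It does not repair the printed definition, which is a stated rule and not an omitted detail.

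**Conclusion.** The point holds as a fault in a stated definition. Seriousness is set by impact on daily life alone, so a bothersome symptom of the treated condition is labelled serious, and the label does not distinguish it from a medically serious event. Most medically serious events would also qualify, but none does so by rule.

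The consequence is misclassification in safety reporting to the principal investigator and the Ethics Committee. Detection of events and the planned incidence test are untouched.

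No number can be put on the mislabelled events. The article gives no rate of new or worsening symptoms and no share that would disturb daily life. The Background section says that bothersome symptoms harm well-being but not how often that would happen among trial participants. It would also be wrong to read the comment that side effects are rarely seen as a count of medically serious events, since it covers side effects and adverse events of the treatments generally.

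The conclusion assumes that the printed definition is the one in use and that no unseen form or manual overrides it. The correction is inexpensive and should be made.

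**What to change.** Amend Adverse event reporting and harms {22} as follows.

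1. Define a serious adverse event by its medical outcome, whatever the cause: death, threat to life, hospital admission or a longer stay, lasting or significant disability, or another important medical event.
2. Apply this to any untoward event and not only to pelvic floor symptoms. This may widen what counts as an adverse event, so the amendment should also say which set of events enters the incidence test.
3. Keep effect on normal daily life as a severity grade in its own field of the Adverse Events Report Form.
4. Re-code the events already recorded among the 75 women enrolled at the first centre. The form's entries for measures taken and outcome should allow this.

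The cost is a wording amendment with Ethics Committee approval, one extra form field and some re-coding, whose volume is unknown because the article gives no event count. No visits or assessments are added. The Trial status section says that applications for the other centres are under way, so a change now would let them start with the corrected definition.
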